## Abstract

The prevalence of symptoms of anxiety is increasing, especially during the COVID-19 pandemic. A home use transdermal neurostimulation device might help to minimize the severity of anxiety disorder. To the best of our knowledge, there is no clinical trial using transdermal neurostimulation to treat individuals with symptoms of anxiety in Asia. This gives us the impetus to execute the first study which aims at evaluating the efficacy of Electrical Vestibular Stimulation (VeNS) on anxiety in Hong Kong. This study proposes a two-armed, double-blinded, randomized, sham-controlled trial including the active VeNS and sham VeNS group. Both groups will be measured at baseline (T1), immediately after the intervention (T2), and at the 1-month (T3) and 3-month follow-up (T4). A total of 66 community-dwelling adults aged 18 to 60 with anxiety symptoms will be recruited in this study. All subjects will be computer randomised into either the active VeNS group or the sham VeNS group in a 1:1 ratio. All subjects in each group will receive twenty 30 min VeNS sessions during weekdays, which will be completed in a 4-week period. Baseline measurements and post-VeNS evaluation of the psychological outcomes (i.e., anxiety, insomnia, and quality of life) will also be conducted on all participants. The 1-month and 3-month follow-up period will be used to assess the long-term sustainability of the VeNS intervention. For statistical analysis, ANOVA with repeated measures will be used to analyze data. Missing data were managed with multiple mutations. The level of significance will be set to *p* < 0.05. Results of this study will be used to determine whether this VeNS device can be considered as a self-help technological device to reduce perceived anxiety in the general population in the community setting. This clinical Trial was registered with the Clinical Trial government, identifier: NCT04999709.

## 1. Introduction

Anxiety is a normal reaction to stress and is considered as an adaptive emotion to help prepare an individual towards perceived threatening situations or stimuli. Nevertheless, exaggerated anxiety without timely treatment may develop into anxiety disorder, which may have detrimental consequences affecting an individual’s quality of life, sleep quality [1], and daily functioning [2]. Before 2020, mental disorders were leading causes of the global health-related burden, with depressive and anxiety disorders being leading contributors to this burden. The COVID-19 pandemic has further increased the global prevalence of anxiety disorders. Nonetheless, there seems to be a lack of robust, novel and non-invasive interventions to reduce the negative detrimental impact caused by COVID-19 pandemic to the community-dwelling populations.

Global prevalence of anxiety disorders during the COVID-19 pandemic

Some researchers conducted a systematic review reporting the global prevalence of anxiety disorders during the COVID-19 pandemic between 1 January 2020 and 29 January 2021 in 204 countries. Two COVID-19 impact indicators, daily SARS-CoV-2 infection rates and reductions in human mobility, were associated with an increased prevalence of anxiety disorders (increase of 25.6% (23.2–28.0)). Females and younger ages were affected more by the pandemic than their male counterparts. It was estimated that anxiety disorders caused 44.5 million (30.2 to 62.5) DALYs globally in 2020 [3]. Recent findings derived from a meta-analytic review [4] also found that the global prevalence of anxiety was 29.57% (95% CI: 24.67–34.47).

Local research findings on anxiety before and during the COVID-19 pandemic

An older local cross-sectional study (Hong Kong Mental Morbidity Survey) (HKMMS) examined the prevalence of common mental disorders (CMD) in 5719 Chinese adults, aged between 16–75, in the general population before the COVID-19 pandemic. Results showed that the weighted prevalence estimate for any past-week CMD was 13.3%, with mixed anxiety and depressive disorder being the most frequent diagnoses. Gender being female, divorced/separated, alcohol misuse/substance dependence, lack of regular physical exercise, and a family history of mental disorder were significant correlates of CMD. Less than 30% of individuals with CMD consulted mental health services [5].

Another population-based local study examined the prevalence of anxiety and depression amidst the COVID-19 pandemic. Of the 500 random samples recruited, 19% had probable depression (PHQ-9 score ≥ 10) and 14% had anxiety (GAD score ≥ 10). In addition, 25.4% reported that their mental health had deteriorated since the pandemic. However, different psychological instruments were used in these studies with different sampling methods; therefore, results need to be interpreted with caution. Notwithstanding the limitations of these studies, it is evident that a significant proportion of Hong Kong citizens are at risk of anxiety during the pandemic era, either those in the medical profession or in the general population. Anxiety is closely linked with depression [6]. Anxiety may also increase sedentary behavior [7], influence arterial pressure, and reduce the activity of individuals’ immune system [8], all of which lead to negative impact on health. Untreated anxiety may spiral easily to depressive symptoms, further increasing the global disease burden and psychiatric morbidity.

The emergence of the coronavirus pandemic has led to the implementation of several precautionary measures across the globe. Hong Kong is of no exception. Hong Kong is one of the world’s densely populated regions, and this possibly explains why the Hong Kong SAR government has enacted stringent quarantine measures and large-scale lockdowns for major entertainment and sports amenities (e.g., amusement parks, public swimming pools, theme parks, etc.). Border closures, social distancing, proper hand hygiene, and compulsory face mask wearing in public, etc., have inevitably increased self-perceived anxiety levels during the pandemic era [9]. As of today, the COVID-19 pandemic in Hong Kong is still an ongoing public health concern, and a significant proportion of Hong Kong citizens are having pandemic fatigue, which increases the odds of COVID-19-related anxiety symptoms [10]. In Hong Kong, low socioeconomic districts were the epicenters of a third-wave outbreak of COVID-19 in July and August 2020, suggesting that people from low socioeconomic classes are vulnerable groups. Socially disadvantaged people are relatively more vulnerable to the physical, mental, and social impacts of infectious diseases. Notably, existing studies were largely cross-sectional, and participants’ narrative comments toward combating the COVID-19 pandemic are under-investigated. Nevertheless, a study [11] interviewed thirty-five economically disadvantaged individuals during the COVID-19 outbreak and examined how these individuals were further disadvantaged in the outbreak by delineating how health inequality intersected with social inequality. Semi-structured interviews were conducted from February to April 2020. Results showed that the soaring prices of disposable surgical face masks and other disinfecting products (hand sanitizer, alcohol preps, disinfectants) alongside other COVID-19-related social distancing policies imposed severe economic and psychological burdens on the participants. All these elements seemed to have interrelated effects which in turn limit accessibility to healthcare, leading to less positive health outcomes.

Existing empirical evidence of the Vestibular Neurostimulation (VeNS)

Since the 20th century, some promising research has demonstrated that VeNS can improve postural stability in patients with Parkinson’s disease [12,13,14], bilateral vestibulopathy [15], or patients of the elderly population [16,17]. Recent VeNS research also showed that repetitive stimulation of the vestibular system may influence hypothalamic control of metabolic homeostasis, and thus decrease fat storage. In other words, VeNS may well be considered as an alternate self-help treatment option for obesity, diabetes, or other related metabolic diseases [18]. Recent findings from meta-analysis also found that there was a positive association between diabetes and anxiety symptoms [19]. Such findings were also echoed by a recent metanalytic review that non-invasive brain stimulation had a significant effect on the reduction of anxiety symptoms [20]. Nonetheless, there seems to be no empirical evidence on the efficacy of VeNS on symptoms of anxiety in Asia, particularly in Hong Kong or China. This research gap has given us the impetus to execute this trial.

Vestibular Neurostimulation (VeNS)—Modius Stress (MS)

Modius Stress (MS) is a non-invasive, transdermal neurostimulation device with a battery-powered headset designed to transcutaneously deliver low-level electrical energy (0–1500 microamperes) to the subject’s head (neurostimulation) to treat anxiety. This MS delivers neurostimulation through two self-adhesive electrode pads which will be placed on the subject’s skin, overlying each mastoid process behind the ear. MS delivers a small electrical impulse which can be adjusted up or down by the subject using the buttons on the headset (max. 1.5 mA at 100 Hz) or via Bluetooth using the mobile app to a level (0–10) where the subject can feel the tingling sensation in the skin (Table 1).

The subject will determine the level of neurostimulation once they begin to experience the gentle swaying, indicating modulation of the vestibular nerve. This device will automatically turn off after 30 min of neuromodulation. The MS device will deliver a small electrical current onto the skin through the electrode pads. This electrical current serves as a neurosignaling waveform which modulates cranial nerves that influence the balance between the parasympathetic and sympathetic nervous systems. MS stimulates the head and vestibular nerves via Cranial Electrotherapy Stimulation (CES).

Cranial Electrotherapy Stimulation (CES) and past research using CES on anxiety

CES is a non-invasive and well-endured neuromodulation treatment that applies pulsed, alternating microcurrent transcutaneously to the head via electrodes placed on the subjects’ earlobes, mastoid processes, zygomatic arches, or the maxilla–occipital junction [21]. CES has been proven to be an effective treatment for anxiety in a study [22] that 83% of the participants (n = 150) had >50% reduction in the Hamilton Rating Scale for anxiety scores after 5 weeks of treatment and co-morbid depression. A recent study also showed that CES stimulation was highly effective on individuals with GAD, with 47.8% remission (n = 161), and a GAD-7 score < 7 after 24 weeks of CES stimulation [23].

A longitudinal follow-up study [24] assessed the effectiveness of vestibular stimulation in the management of stress in twelve female gastric ulcers patients who were given six months of vestibular stimulation. Results showed that these participants’ depression, anxiety, and stress levels were significantly decreased after 3 months of vestibular stimulation (*p* < 0.05) when compared with baseline scores, and these instrumental scores further decreased after 6 months of intervention (*p* < 0.05), indicating that vestibular stimulation is a long-term sustainable intervention in the management of gastric ulcers. Apart from VeNS and CES, Galvanic Vestibular Stimulation (GVS) is another non-invasive stimulation acting on the vestibular system.

Galvanic Vestibular Stimulation (GVS)

GVS is also a non-invasive method used to stimulate the vestibular system. The vestibular system includes the sensors, neural pathways, vestibular nuclei, and the cortical areas receiving integrated vestibular inputs. The key role of the vestibular system is in postural control or gaze stabilization and involves some cognitive functions and emotion processing. Nevertheless, GVS is known to induce motion sickness symptoms such as nausea. Several studies have revealed a modulating effect of vestibular stimulation on anxiety levels. For example, a study [25] evaluated the tolerability and efficacy of a GVS protocol on anxiety and tested the impact of stimulation parameters (duration) on anxiety. Twenty-two students underwent three stimulation conditions: (1) a sham session with no stimulation; (2) 38 min of GVS; and (3) 76 min of GVS. Results showed a significant diminution in anxiety levels for the second group (those receiving a 38-min session of GVS), while a low level of motion sickness was reported for the third group (those receiving a 76-min session of GVS). In this trial, we will focus on the efficacy of VeNS in the treatment of anxiety symptoms in the general population.

### 1.1. Objectives

The aims of this study are (1) to evaluate the efficacy of VeNS on anxiety severity on community-dwelling adults in Hong Kong and (2) to examine the association between VeNS data usage, anxiety symptom severity, insomnia severity, and quality of life.

### 1.2. Hypotheses

#### 1.2.1. Primary Hypothesis

Participants in the active VeNS group will have at least a 50% reduction in their (General Anxiety Disorder-7) (GAD-7) score after four weeks of treatment, and this will be maintained for the 12-week follow-up. However, participants in the sham VeNS group will have a <5% reduction in their GAD-7 score after the 4-week treatment and during the 12-week follow-up.

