## 2. Materials and Methods

### 2.1. Trial Design

This is a four-week VeNS treatment on anxiety among adults in the general population. The trial design complies with the Consolidated Standards of Reporting Trials (CONSORT) statement [26]. Participants will be randomized into the active VeNS or sham VeNS group. All the participants will be informed about the randomization procedures and that they have a 50% chance of receiving the VeNS or the sham VeNS. This study will be conducted in accordance with the Declaration of Helsinki [27]. Both groups will be measured at the baseline (T1), immediately after the 4-week intervention (T2), and during a 3-month follow-up (T4) [23,28] (see Figure 1).

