### 2.2. Subjects and Sample Size Estimation

Since the collaborative UK study is ongoing, we thus have to take reference of a similar CES study on GAD [23] on ‘Clinical effectiveness and cost minimization model of Alpha-Stim cranial electrotherapy stimulation in treatment seeking pts with moderate to severe GAD’. Participants in the CES group had a significant reduction in GAD-7 score (from baseline 15.77 (3.21) to 10.14 (4.86) (Cohen’s *d* = 1.3)) after 4 weeks of CES treatment.

Considering this trial is a sham-controlled trial, we hypothesize a large effect in the MS group. We used G*power version 3.1.9.7 (https://stats.oarc.ucla.edu/other/gpower/) (accessed on 1 April 2022) nto calculate the target sample size. With a statistical power of 99% and a statistical significance level at 0.05 to detect a large between-groups effect size of 1.3, each group will require 33 subjects. With an estimated attrition rate of 30% during the 12-week post-treatment follow-up, a total sample of 66 is required in this trial.

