## 3. Statistical Analyses

All statistical analyses will be performed using the statistical software R for Windows (R version 4.1.0). Means and standard deviations (SD) for the continuous variables will be presented, while numbers and percentages for the categorical variables will be shown. A *p*-value < 0.05 is considered statistically significant. Sociodemographic differences between the VeNS group and the sham VeNS group will be analyzed using the chi-square test and t-test. If there are significant differences between sociodemographic factors, covariates will be considered as confounding variables in the analyses. Normality of the primary outcome (GAD-7) scores will be tested using the Shapiro–Wilk test for each combination of factor levels (group and time). A t-test will be used to test the baseline difference. Analysis of variance (ANOVA) with repeated measures will be used to test the group (between-subject factor), time (within-subject factor), and group x time interaction effects of the GAD-7 score between the VeNS group and the sham VeNS group. Post hoc comparisons between groups and time points will be conducted using a *t*-test with the Bonferroni correction. Normality of the secondary outcome scores will be tested using the Shapiro–Wilk test for each time point. For normally distributed outcomes, ANOVA with repeated measures will be used to determine whether the outcome scores are significantly different between pre-and post-test periods. For outcome scores that are normally distributed, a non-parametric Friedman test will be used to test the mean difference. A Cohen’s d effect size for each outcome will be calculated, where d = 0.2, 0.5, and 0.8, corresponding to small, medium, and large effect sizes, respectively. Participants’ total usage time will also be used to investigate the effectiveness of the VeNS on anxiety and total usage time will be used as a continuous covariate in a linear regression model for GAD-7 total score. Missing data will be managed with multiple imputation [36] by adopting the last observation carried forward (LOCF) method.

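### The primary hypothesis is two within-arm percentage thresholds that the planned analysis does not test, and the 50% threshold exceeds the 35.7% drop used to size the trial

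*Protocol article*

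**What the plan says.** Section 1.2.1 gives the only primary hypothesis. It has two parts, one per arm. The "active VeNS group will have at least a 50% reduction in their (General Anxiety Disorder-7) (GAD-7) score after four weeks of treatment", with the effect kept through the 12-week follow-up, while "participants in the sham VeNS group will have a <5% reduction in their GAD-7 score" at the end of treatment and during follow-up. It states no difference between arms.

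Section 3 plans a repeated-measures ANOVA, "used to test the group (between-subject factor), time (within-subject factor), and group x time interaction effects of the GAD-7 score", comparing the two groups, followed by t-tests between groups and time points with Bonferroni correction. It defines no percentage change and no responder variable for GAD-7.

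Section 2.2 takes its planning evidence from a cranial electrotherapy study whose treated group moved "from baseline 15.77 (3.21) to 10.14 (4.86" after four weeks, and sizes the trial "to detect a large between-groups effect size of 1.3, each group will require 33 subjects".

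On visits, the Abstract lists baseline, "immediately after the intervention (T2), and at the 1-month (T3) and 3-month follow-up (T4"; Section 2.1 lists baseline, "immediately after the 4-week intervention (T2), and during a 3-month follow-up (T4", with no T3.

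**The concern.** A primary hypothesis should be a statement that the primary test can support or reject. Here the two do not meet. The hypothesis concerns the size of the percentage fall within each arm. The ANOVA effects and the post hoc t-tests all ask whether a difference is zero. A significant interaction would not show that active fell by 50% or that sham fell by less than 5%, and a non-significant one would not refute either statement.

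Two things follow. First, the stated hypothesis and the planned test can give opposite answers from the same data. Second, three effects are listed with none marked as decisive, and they are not equivalent. The group x time effect addresses whether VeNS changes GAD-7 more than sham does. The group main effect averages in the baseline visit. The time main effect can be significant when both arms improve equally, so it cannot bear on efficacy.

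The 50% figure also sits uneasily with the plan's own evidence, because the sizing study did not reach it.

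**Working it through.** **Inputs.** From Section 2.2: baseline mean 15.77 (SD 3.21), four-week mean 10.14 (SD 4.86), effect size 1.3, power 99%, significance level 0.05, attrition 30%. From Section 1.2.1: thresholds of 50% and 5%. Assumed, because the document does not give them: pre-post correlation r of 0.3 to 0.5, and a true sham drop of 10% in step 5.

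**1. The plan's own sample size.** A two-sided two-sample t-test with d = 1.3 and 99% power needs 23 per arm (exact power 0.9906). Allowing for attrition, 23/(1 - 0.30) = 32.9, so 33 per arm and 66 in total. The stated figure reproduces. The checks below use 23 (completers) and 33 (all randomised) per arm.

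**2. The reference result against the 50% threshold.**
- Reference drop: 15.77 - 10.14 = 5.63 points; 5.63/15.77 = 35.7%.
- A 50% drop from 15.77 is 7.885 points. The shortfall is 7.885 - 5.63 = 2.255 points.

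**3. Chance of observing a 50% mean drop if the truth is the reference result.** SD of change = sqrt(3.21² + 4.86² - 2 x r x 3.21 x 4.86); standard error = SD/sqrt(n); z = 2.255/standard error.

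| r | SD of change | n | z | Probability |
|---|---|---|---|---|
| 0.3 | 4.96 | 23 | 2.18 | 1.46% |
| 0.3 | 4.96 | 33 | 2.61 | 0.45% |
| 0.5 | 4.28 | 23 | 2.53 | 0.58% |
| 0.5 | 4.28 | 33 | 3.03 | 0.12% |

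The range is about 0.1-1.5%. This holds the threshold at 7.885 points, that is, half of the reference baseline.

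**4. What the two thresholds imply between arms.** At a baseline of 15.77, at least 50% against less than 5% means a gap of more than 0.45 x 15.77 = 7.10 points. Divided by the root mean square of the two reference SDs, sqrt((3.21² + 4.86²)/2) = 4.12, that is d = 1.72. Divided by the follow-up SD of 4.86, it is d = 1.46. Both exceed the 1.3 used for sizing.

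**5. Can the planned comparison succeed while the hypothesis fails?** Take active at the reference drop and sham at an assumed 10% drop (1.577 points). The gap is 5.63 - 1.577 = 4.05 points. A two-sided two-group t-test then has these powers:

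| SD | d | n = 23 per arm | n = 33 per arm |
|---|---|---|---|
| 4.12 | 0.98 | 90% | 98% |
| 4.86 | 0.83 | 79% | 92% |

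In this scenario both true values miss their thresholds (35.7% is below 50%, and 10% is not below 5%), yet a between-arm comparison would usually be significant. The calculation applies the reference study's baseline and SDs to both arms.

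**The case against.** The strongest reply is that the percentages are predictions, not a decision rule. Nothing in the document says the trial fails if active falls by less than 50%. Sections 1.1 and 2.12 state the aim as evaluating efficacy, and Section 3 does plan a group x time test between active and sham. Much of this stands. A reader might infer that no between-arm test is planned, or that an effective device would be declared ineffective. The document supports neither, and step 5 shows that a between-arm comparison could well detect a benefit. A reader might also infer that the time effect would be reported as the main result. The text leaves the deciding effect open but does not say that.

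It can also be said that naming one contrast is often left to an analysis plan, and that Section 1.2.1 does order the time points (four weeks, then maintenance). That weakens any complaint about missing detail. It does not remove the mismatch, because the hypothesis that is written is not one that the written tests address.

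The 35.7% comes from a different device in treatment-seeking patients, used because the UK study was still running. The Introduction cites another electrotherapy study in which 83% of participants had more than a 50% reduction, but on the Hamilton scale at five weeks and not used for sizing. So the evidence cited is not uniformly below 50%; only the sizing result is.

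The 50% could also mean each participant's own reduction rather than the group mean. The probabilities in step 3 apply only to the group-mean reading. The planned tests address neither reading.

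Finally, one might argue that a sham drop under 5% is implausible because entry requires a raised GAD-7 and scores would regress to the mean. The document gives no retest correlation or sham data from which to size that effect, so it is not claimed here.

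**Conclusion.** The mismatch is established from the text alone: Section 1.2.1 sets two within-arm thresholds, and no test in Section 3 addresses them. On the group-mean reading, the 50% threshold exceeds the 35.7% result used for sizing. An active arm that truly matched that result would show a 50% mean drop in about 0.1-1.5% of trials. That range rests on the reference SDs, an assumed correlation of 0.3-0.5 and 23-33 analysed per arm.

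The consequence is that a significant benefit over sham and failure of the stated primary hypothesis can occur together, with no rule in the document for which one is the trial's answer. The sample-size arithmetic is not in dispute.

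The difference in visits is a separate inconsistency. The Abstract has four assessments, while Sections 2.1, 2.11 and 2.12 each describe three. It matters here because the number of levels of the time factor sets the interaction's degrees of freedom and the number of post hoc comparisons. The document does not show which schedule is intended.

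**What to change.** - **Section 1.2.1:** restate the primary hypothesis as a difference between active and sham in GAD-7 at T2.
- **Section 3:** amend to match. Name one primary test: either the group x time contrast at T2 from the repeated-measures model, or a baseline-adjusted comparison of the arms at T2. If the second is chosen, say that it replaces the ANOVA as the primary test; otherwise a new mismatch is created. Make T4 secondary and the time main effect descriptive only.
- **Percentages:** keep a reduction of at least 50% as a secondary responder outcome, defined per participant and compared between arms. Drop the 5% sham figure as a criterion, or label it an expectation.
- **Visits, separately:** reconcile the Abstract with Sections 2.1, 2.11 and 2.12, so that the levels of the time factor are fixed.

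The cost is an amendment to the hypothesis and to the analysis section, preferably before unblinding. The hypothesis and analysis changes need no new participants or measurements. Whether the visit reconciliation alters data collection depends on which schedule is in use.
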